## 12.2 Objectives of the translational study

- 1.- Assess the expression of CDK4 (and p16INK4A) mRNA and protein in tumor samples from patients diagnosed with sarcoma (blood and paraffin block), to identify the most reliable and effective method to select CDK4 and/or p16INK4A as a predictive biomarker of the efficacy of palbociclib.
- 2.- Evaluate the predictive and/or prognostic value, at the mRNA and protein level, of p53, p21CIP1, p27KIP1, Rb, FoxM1 and cyclin D1 as potential biomarkers of the efficacy of palbociclib, in blood samples and in paraffin blocks (pre- and post-treatment).
- 3.- Analyze other senescence markers (combination of Ki67 negative with high density (>5 per nucleus) of γH2A.X) by immunohistochemistry of paraffin blocks (pre- and post-treatment). Pre- and post-treatment samples from each patient will be compared to determine senescence induced by palbociclib treatment.
- 4.- Correlate biomarkers that are predictive of palbociclib efficacy with clinical outcomes, such as PFS, OS and clinical benefit rates (complete response, partial response and stable disease).
- 5.- Evaluate the effect of palbociclib in modulating the immune response in paraffin block samples from patients undergoing chemotherapy. The evaluation will be performed on pre- and post-treatment samples from each patient.

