## 4. PATIENT SELECTION

### 4.1 Inclusion criteria

#### Cohort 1 (first phase) – STS and BS

- 1) CDK4 overexpression (mRNA expression) and low or normal p16 expression (mRNA expression) measured in paraffin tumor samples at study entry.
- 2) ECOG 0-1 at the moment of enrollment.
- 3) Diagnosis of soft tissue sarcoma or bone sarcoma (in both cases with metastasis or locally advanced inoperable).
- 4) Documented disease progression during the 6 months prior to study entry.
- 5) Patients must have the following laboratory results:
  - Absolute neutrophil count  $\geq 1,500/\text{mm}^3$  ( $1.5 \times 10^9/\text{L}$ );
  - Platelets  $\geq 100,000/\text{mm}^3$  ( $100 \times 10^9/\text{L}$ );
  - Hemoglobin  $\geq 9 \text{ g/dL}$  ( $90 \text{ g/L}$ );
  - Blood creatinine level  $\leq 1.5 \times \text{ULN}$  or estimated creatinine clearance  $\geq 60 \text{ mL/min}$ ;
  - Total level of blood bilirubin  $\leq 1.5 \times \text{ULN}$  ( $\leq 3.0 \times \text{ULN}$  if Gilbert's disease);
  - AST and/or ALT  $\leq 3 \times \text{ULN}$  ( $\leq 5.0 \times \text{ULN}$  if liver metastasis is present);
  - Alkaline phosphatase  $\leq 2.5 \times \text{ULN}$  ( $\leq 5.0 \times \text{ULN}$  if bone or liver metastases are present);
- 6) Patients must have signed written consent to participate in the clinical study, and to provide at least two tumor blocks in paraffin for molecular analyses in the screening phase.
- 7) Biopsy at baseline if there are no archive tumor samples obtained in the 3 months prior to the start of treatment.
- 8) Patients must have received standard treatments for at least one, two or three lines for advanced disease.
- 9) Age between 18 and 80 years (both ages included).
- 10) Measurable disease according to RECIST 1.1 criteria.
- 11) All patients (men and women) of childbearing age must use an effective method of contraception throughout treatment with palbociclib and for at least 90 days after the last dose. Pregnancy must be ruled out by urine or blood test (negative pregnancy test) for inclusion in the study. Men should be advised to consider sperm preservation before starting treatment due to the risks of infertility.

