### ***CDKN2A mutation verification (chordoma cohort)***

In order for patients to participate in the trial, documentation confirming the CDKN2A mutation must be provided.

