## 11. STUDY DESIGN AND STATISTICS

### 11.1 Study design

GEIS-51 is a multicenter, open-label, non-randomized, phase II clinical trial that initially had a single cohort of advanced sarcomas with CDK4 overexpression. Subsequently, a second phase (additional cohort) focused only on chordomas has been included. The study will be conducted only in Spain including the participation of third level hospitals.

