| 5  | Tumor          | Paraffin block | At the end of treatment with palbociclib                                                                                                                                                                     | 1 block  | Optional       |                                                           |                                                              |
| 6  | Blood          | Blood tube     | Baseline (within 72h prior to initiation of palbociclib treatment)                                                                                                                                           | 25 ml    | Obligatory     |                                                           |                                                              |

|   |       |            |                                                                        |       |            |  |  |
|---|-------|------------|------------------------------------------------------------------------|-------|------------|--|--|
| 7 | Blood | Blood tube | Within 72h after completion of the first cycle of palbociclib (day 28) | 25 ml | Obligatory |  |  |
| 8 | Blood | Blood tube | After each radiological evaluation                                     | 25 ml | Obligatory |  |  |

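### Translational objectives 1, 2 and 4 aim at predictive biomarkers, which single-arm palbociclib cohorts cannot identify, and objective 2 draws part of that value from optional end-of-treatment blocks

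*Protocol*

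**What the plan says.** On design, section 11.1 states: "GEIS-51 is a multicenter, open-label, non-randomized, phase II clinical trial that initially had a single cohort of advanced sarcomas with CDK4 overexpression". The chordoma cohort was added later. Both cohorts receive palbociclib, and no control, untreated or marker-negative group is described.

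On entry, cohort 1 (section 4.1) requires "CDK4 overexpression (mRNA expression) and low or normal p16 expression (mRNA expression) measured in paraffin tumor samples at study entry". For cohort 2, section 7.3 says that "documentation confirming the CDKN2A mutation must be provided".

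On aims, three of the five objectives in section 12.2 use the word predictive:

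- Objective 1 measures CDK4 and p16 mRNA and protein "to identify the most reliable and effective method to select CDK4 and/or p16" as a predictive biomarker of palbociclib efficacy.
- Objective 2 is to "Evaluate the predictive and/or prognostic value, at the mRNA and protein level", of p53, p21, p27, Rb, FoxM1 and cyclin D1. Its materials are given as "in blood samples and in paraffin blocks (pre- and post-treatment".
- Objective 4 takes biomarkers already called predictive and correlates them with PFS, OS and clinical benefit.

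On samples, Table 5 in section 12.3 times the post-treatment block "At the end of treatment with palbociclib" and marks it optional. Section 12.4.1 adds that such samples come only from patients who accept the procedure. The baseline block, the pre-treatment blood and the day-28 blood are obligatory. Section 4.3 lists RECIST progression first among the reasons for stopping treatment. The analytical methodology in section 11.3 relates markers to clinical response by standard regression and correlation, with no rule on when the marker must have been measured.

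**The concern.** A predictive marker is one whose level changes the effect of the drug. That is a treatment-by-marker interaction, and estimating it needs patients who do not receive the drug. With one treated arm, a marker that merely tracks the natural course of the disease looks the same as one that identifies patients who benefit.

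The protocol contains a concrete example. Section 12.1 reports that p53 mutation appears related to worse PFS and OS in advanced soft tissue sarcoma, citing a randomised trial of trabectedin plus doxorubicin against doxorubicin. p53 is one of the objective 2 markers. A link between p53 and PFS here could repeat that prognostic effect and be reported as predictive of palbociclib efficacy.

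The end-of-treatment block adds a second problem. If it is taken at progression, the length of PFS decides how long the tumour was exposed to the drug before sampling. Any marker that moves with time on drug can then correlate with PFS without carrying information about it. Movement on drug is plausible from section 12.1 itself, which says that palbociclib lowers tumour CDK4 and acts on the phosphorylation that stabilises FoxM1.

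**Working it through.** **What the plan quantifies.** No sample size is stated for the translational objectives. The numbers available come from the two Simon designs in section 11.3. These reproduce: cohort 1 (at least 3 of 15, then at least 6 of 21; 15% against 40%) has type 1 error 0.081 and power 0.900. Cohort 2 (at least 3 of 9, then at least 9 of 19; 30% against 60%) has 0.081 and 0.903. Both keep to the stated 10% limits. At most 21 + 19 = 40 patients are available, all treated.

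**Identifiability.** Let T+ and T− be the 6-month PFS rates of treated marker-positive and marker-negative patients, and U+ and U− the rates the same groups would have untreated. Then

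T+ − T− = [(T+ − U+) − (T− − U−)] + (U+ − U−).

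The bracket is the predictive part and the last term the prognostic part. The trial observes only the left side. With assumed treated rates of 60% and 20%, the left side is 40 points, and two opposite truths fit it:

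| Assumed truth | U+ | U− | Drug effect, positive | Drug effect, negative | Predictive part | Prognostic part |
|---|---|---|---|---|---|---|
| Purely prognostic | 40% | 0% | 60 − 40 = 20 | 20 − 0 = 20 | 0 | 40 |
| Purely predictive | 15% | 15% | 60 − 15 = 45 | 20 − 15 = 5 | 40 | 0 |

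More patients would estimate the 40 points better but would never split them.

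**Range of the markers.** Selection acts on CDK4 and p16 mRNA in cohort 1 and on CDKN2A, the gene for p16, in cohort 2. It therefore bears on objective 1. It does not act directly on the six objective 2 markers. CDK4 is not an inclusion criterion in cohort 2, and section 2.2 reports varied CDK4 mRNA in chordoma (7 high, 1 intermediate and 2 low of 10).

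**End-of-treatment samples.** The size was gauged by simulating 4000 trials per setting. All settings are assumptions:

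- PFS is exponential with 45% progression-free at 6 months, midway between the cohort 2 hypotheses: (30 + 60)/2. The monthly hazard is −ln(0.45)/6 = 0.133.
- The baseline marker is N(0,1) and independent of PFS.
- End value = baseline + d × PFS/6 + N(0, SD 0.3), with PFS capped at 24 months for the drift and d in SD per 6 months. The block is taken at progression.
- The test is Spearman correlation with PFS at two-sided 5%.

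| Blocks | d = 0.25 | d = 0.5 | d = 1 |
|---|---|---|---|
| 19 | about 15% | about 42% | about 86% |
| 10 | about 10% | about 22% | about 53% |
| 6 | about 8% | about 13% | about 29% |

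With 19 blocks the mean correlation is 0.21, 0.40 and 0.63 across the three drifts, while the baseline value is significant in 5% of trials, as it should be. If the marker instead shifts by 1 SD early and then levels off (time constant 0.5 months), the end value is significant in about 7% with 19 blocks.

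**The case against.** The strongest reply is that the protocol never says end-of-treatment values will be regressed on PFS. Objective 2 lists materials. Where a use for paired samples is spelled out, it is comparison before and after treatment: objective 3 for senescence, objective 5 for immune response, and section 12.4.2 for blood RNA. Which sample enters which model is commonly settled in a statistical analysis plan, which is not shown. This stands in part. A reader might infer that a flawed regression is planned, and the text does not support that. It does support something narrower: objective 2 ties predictive or prognostic value to post-treatment blocks, and nothing in section 11.3 excludes that use.

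The second reply concerns the size. Nineteen blocks would require every chordoma patient to accept an optional biopsy, no drift rate or shape is documented, and treatment can also end before progression, with imaging continuing under section 7.7. All of this stands. The figure of about 86% is the extreme of an assumed range and is not a forecast for this trial.

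The third reply is that objective 2 says and/or prognostic, speaks of potential biomarkers, and feeds no decision rule. That softens objective 2 but not objectives 1 and 4. Section 12.2 does not call the work exploratory. Section 3.2 lists the correlation of clinical data with molecular variables as a secondary objective, and section 15.5 foresees separate publication.

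**Conclusion.** The wording of objectives 1, 2 and 4 promises more than the design can give. Without a comparator, the substudy can show association with outcome under palbociclib but not predictive value. This rests on the design alone and needs no assumed figure. The narrowed range of CDK4 and p16 mRNA in cohort 1 and of CDKN2A in cohort 2 is an added limit on objective 1.

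The end-of-treatment point is narrower. It concerns the optional block set against PFS, response or clinical benefit when treatment stopped for progression. False-positive rates there run from near nominal to severe, depending on the number of blocks and the shape of the drift, and are illustrative only.

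A reader might go further and infer that all the marker data are measured after the outcome, or that every marker is truncated. Neither follows. The timing problem does not reach OS, baseline samples, day-28 blood, or stops before progression, and selection does not act directly on the six objective 2 markers. The before-and-after comparisons in objectives 3 and 5 stand. The primary endpoint and the Simon decision rules are untouched.

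**What to change.** 1. Reword objectives 1, 2 and 4 as the association of markers with 6-month PFS, PFS, OS and clinical benefit in palbociclib-treated patients, and state that predictive and prognostic effects cannot be separated in this design.
2. Base outcome associations on the baseline block and the pre-treatment blood. Use the day-28 blood only in a landmark analysis that starts at day 28, among patients still at risk then.
3. In objective 2, limit end-of-treatment blocks to within-patient change, as objective 3 already does, and report how many patients have both samples.

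The cost is a change of wording and a landmark rule. No new samples, visits or patients are needed. The sponsor gives up the label predictive.

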## 12.3 Collection of biological samples

The samples to be collected in the study are described in the following table:

| Nº | Type of sample | Contained in   | Time of collection                                                                                                                                                                                           | Quantity | Enforceability | Purpose                                                   | Destination and person in charge                             |
|----|----------------|----------------|--------------------------------------------------------------------------------------------------------------------------------------------------------------------------------------------------------------|----------|----------------|-----------------------------------------------------------|--------------------------------------------------------------|
| 1  | Tumor          | Paraffin block | Already existing (biopsy or previous surgery)                                                                                                                                                                | 1 block  | Obligatory     | First analysis of-CDK4 and p16 expression (pre-screening) | Instituto Biomedicina Sevilla – [name]          |
| 2  | Tumor          | Paraffin block | Before enrollment                                                                                                                                                                                            | 1 block  | Obligatory     | CDK4 and p16 expression confirmation                      | CITIUS III – [name] [name]                        |
| 3  | Tumor          | Paraffin block | Already existing (biopsy or previous surgery)                                                                                                                                                                | 1 block  | Obligatory     | Central confirmation of diagnosis                         | Hospital Universitario Virgen del Rocío – [name] |
| 4  | Tumor          | Paraffin block | Within 28 days prior to the start of treatment (if new) or within 3 months prior to the start of treatment (if already biopsied, in the absence of systemic treatment from collection to start of treatment) | 1 block  | Obligatory     | Translational substudy                                    | CITIUS III – [name] [name]                        |
| 5  | Tumor          | Paraffin block | At the end of treatment with palbociclib                                                                                                                                                                     | 1 block  | Optional       |                                                           |                                                              |
| 6  | Blood          | Blood tube     | Baseline (within 72h prior to initiation of palbociclib treatment)                                                                                                                                           | 25 ml    | Obligatory     |                                                           |                                                              |

|   |       |            |                                                                        |       |            |  |  |
|---|-------|------------|------------------------------------------------------------------------|-------|------------|--|--|
| 7 | Blood | Blood tube | Within 72h after completion of the first cycle of palbociclib (day 28) | 25 ml | Obligatory |  |  |
| 8 | Blood | Blood tube | After each radiological evaluation                                     | 25 ml | Obligatory |  |  |

**Table 5: Biological samples of the trial**

## 12.4 Methods and experiments

### 12.4.1 Protein evaluation

#### 1) *Building of tissue microarrays (TMA)*

Four tru-cut biopsies (12G cylinders) will be compulsorily obtained at the time of diagnosis, which will be included in two paraffin blocks. In addition, post-treatment samples (two blocks) will be collected from a selective number of patients who accept the procedure. All cases will be reviewed by expert sarcoma pathologists. The blocks will be sent to the central translational laboratory, together with an anonymized copy of the pathology report. Hematoxylin-eosin (H&E) staining will be performed on each block in order to verify the existence of the tumor and thus select two representative areas.

Protein expression will be evaluated by immunohistochemical methods after the production of a tissue microarray (TMA) from pre- and post-treatment paraffin blocks. This method consists of carefully and simultaneously placing a high number of samples in a paraffin-embedded tissue. This allows the processing of a large number of samples under the same technical conditions. Whenever possible, two different tumor regions will be studied in each block. 3 µm sections will be obtained from each of the TMAs for immunohistochemical tests. Antibodies against the following proteins will be used: CDK4, p16ink4a, p53, p21CIP1, p27KIP1, Rb, FoxM1, cyclin D1, Ki67 and γH2A.X. NK cell infiltrations will also be detected by immunohistochemistry with an anti-CD335 antibody (NKp46) and macrophages with an anti-CD68 antibody. A template will be prepared to ensure correct identification of each sample in the array.

#### 2) *Immunohistochemistry*

Immunohistochemical studies will be performed on formalin-fixed, paraffin-embedded tissues, using 3-4 µm sections for this purpose in all cases. These studies will be done when inclusion of the tumor specimen in a TMA is not possible. The same antibodies described in the construction of tissue microarrays (TMA) will be used in the immunohistochemical studies.

**Note:** To improve the reliability of the immunohistochemical analysis, the results will be made by two pathologists. Additionally, complete block samples (one sample per 5 cases) will be reviewed in order to validate the results.

### 12.4.2 Transcriptional evaluation

#### 1) *RNA expression from paraffin-embedded tissue samples*

RNA will be extracted and purified from paraffin blocks, and validation of individual genes will be performed by *qRT-PCR*. Total RNA will be isolated with the Recover All Total Nucleic Acid Isolation® kit (Ambion), according to the manufacturer's protocol, and 40 ng of total RNA will be used for reverse transcription using the High Capacity cDNA Reverse Transcription Kit (Applied Biosystems™ - Thermo Fischer Scientific), in the presence of MultiScribe™ reverse transcriptase and a random primer scheme to initiate cDNA synthesis. The cDNA obtained will be amplified and quantified by quantitative PCR using the TaqMan® Fast Advanced Master Mix Kit (Thermo Fischer Scientific). The relative expression of target genes will be normalized to β2-microglobulin (β2M: (Hs99999907\_m1, Applied Biosystems) and the expression in each sample will be compared to the control (RNA pool: Universal Human Reference RNA; Agilent Technologies). Individual quantification of gene expression will be performed by comparative CT (CT) method and relative expression will be calculated as 2-ΔCT. Genomic analysis includes the cyclin-dependent kinase *CDK4*, the cell cycle inhibitors *CDKN1A* (p21CIP1), *CDKN2A* (p16ink4a), *CDKN1B* (p27KIP1), the tumor suppressor proteins *TP53* and *RB*, the cell cycle regulatory protein *CCND1* (cyclin D1), and the transcription factor *FOXM1*.

#### 2) *RNA expression from peripheral blood samples*

Blood samples will be collected in EDTA tubes (2 x 10 ml per draw) at these times: (i) within 72 hours prior to initiation of palbociclib treatment, (ii) at the end of the first cycle (day 28) of palbociclib treatment, and (iii) after each radiological evaluation. After collection, blood samples will be stored at room temperature and sent within 24 hours to the central translational laboratory where the tubes will be stored at -20°C or -80°C, until use. RNA will be extracted from blood samples with the PAXgene RNA Kit Blood (PreAnalytiX). Reverse transcription, qRT-PCR and analysis of results will be carried out as described in point 1 of this section (Transcriptional evaluation). The same genes specified in point 1 of this section will be evaluated and the results obtained between pre- and post-treatment samples will be compared.

All samples from the translational substudy should be sent to the following address:

**CITIUS III - [name]  
University of Seville  
[name]  
[name]**

For questions related to the shipment or collection of samples, please contact:

### 13. ETHICAL AND REGULATORY ASPECTS

#### 13.1 Ethics committee

The trial protocol and related documents will be submitted for review to the ethics committee, in accordance with the applicable regulations, prior to the start of the trial. Approval by the ethics committee is essential for initiation of the study.

#### 13.2 Competent authority

The trial protocol and related documents should be submitted to the competent authority prior to the start of the clinical trial, as required by the Spanish Agency of Medicines and Medical Devices (AEMPS) of Spain. The approval of the AEMPS is indispensable for the initiation of the study.

